## Abstract

**Background:**

In Pakistan, one-third of under-5 deaths (58/1000 live births) are attributable to the high prevalence of stunting (40%), underweight (23%), and wasting (17.7%). Given the suboptimal prevalence of exclusive breastfeeding (EBF; 48%) and the alarmingly low consumption of a minimum acceptable diet (3.6%), mitigation of early-life nutritional risk provides a critical window of opportunity for intervention. Mobile health (mHealth) provides an innovative and low-cost option to improve infant and young child feeding practices (IYCFPs) among mothers.

**Objective:**

This study aims to assess the efficacy of a context-specific mHealth coaching app in promoting EBF and IYCFPs compared to face-to-face (F2F) counseling.

**Methods:**

This is a prospective, parallel-arm randomized controlled trial planned at a secondary care hospital in Karachi, Pakistan. The study will enroll 300 booked singleton pregnant women in the third trimester, who plan to stay in their respective areas for at least 1 year postdelivery, are registered for child immunization at the associated Family Health Center, own smartphones with internet access, are able to read Urdu, and provide consent. Participants in the intervention arm will receive the *Pehli Ghiza* mHealth app along with routine standard-of-care F2F counseling. The app will deliver context-specific educational content on breastfeeding and IYCFPs through short videos and messages sent 3 times per week, tailored to the stage of pregnancy and infant age. Participants in the control arm will receive only routine F2F counseling. The standard of care will be delivered at each follow-up visit, which is scheduled at birth, at 6, 10, and 14 weeks, and at 6, 9, and 12 months of the infant’s age. Data will be collected at enrollment and at each follow-up visit using structured questionnaires. Primary outcomes are EBF and the introduction of age-appropriate complementary feeding. Secondary outcomes include early initiation of breastfeeding, continued breastfeeding at 1 year, minimum dietary diversity, meal frequency, minimum acceptable diet, and child health outcomes. Analysis will follow the intention-to-treat principle to detect a 20% absolute improvement in primary outcomes between the intervention and control groups over time and to evaluate between-group differences in feeding practices. Compliance will be determined by the proportion of participants who complete the 6-month coaching program. Usability will be assessed based on features related to design, interface, content, coaching, perception, and personal benefit.

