#### Message Schedule

Messages will be delivered 3 times per week, beginning in the predelivery period and continuing until the child reaches 12 months of age. This schedule ensures continuous exposure to age-appropriate information during pregnancy and early infancy.

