#### User Engagement Metric

A set of engagement indicators will be derived from *MixPanel* mobile analytics [47], including video view counts, module completion status, time spent on each module, and frequency of app access. These metrics will provide an objective, time-stamped record of participant interaction with the intervention, enabling assessment of both the intensity and pattern of exposure over time.

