#### Intervention Fidelity Assessment

The user engagement indicators will be used to assess intervention fidelity by evaluating the extent of participant exposure and adherence to the intervention as intended. Fidelity will be evaluated through cumulative exposure to scheduled content, the proportion of modules completed, and the average duration of interaction with intervention components. Based on predefined thresholds, participants will be categorized into fidelity groups as high (≥70% of scheduled content viewed and ≥70% of modules completed), moderate (40%‐69% of scheduled content viewed), and low (<40% of scheduled content viewed) fidelity [48]. These fidelity classifications will allow examination of dose-response relationships between intervention exposure and primary outcomes and will help interpret the effectiveness of the intervention in relation to varying levels of engagement.

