### Outcome Measures

#### Outcome Assessment and Schedule

The outcome indicators are derived from WHO IYCF indicators [49,50]. Outcome data will be collected using structured interviewer-administered questionnaires and anthropometric assessments at predefined follow-up visits. The schedule of outcome measurements is presented in Table 2.

**Table 2. T2:** Schedule of enrollment, interventions, and assessments of participants as per SPIRIT (Standard Protocol Items: Recommendations for Interventional Trials).

Study steps	Baseline	Postallocation						
		Birth	6 wk	10 wk	14 wk	6 mo	9 mo	12 mo
Enrollment and allocation								
Eligibility screen	✓^a^							
Informed consent	✓							
Randomization	✓							
Allocated intervention								
mHealth^b^ coaching	mHealth coaching will occur continuously across the study period with the SoC^c^, not just at specific time points							
Face-to-face counseling	✓	✓	✓	✓	✓	✓	✓	✓
Participants characteristics								
Maternal	✓							
Infant		✓						
IYCF^d^ knowledge, attitude, and breastfeeding self-efficacy								
Baseline (at enrollment)	✓							
Midline (14th wk)					✓			
Endline (12th mo)								✓
Study outcome								
Early initiation of breastfeeding		✓						
Exclusive breastfeeding^e^			✓	✓	✓	✓^e^		
Continuation of breastfeeding at 1 y			✓	✓	✓	✓	✓	✓
Introduction of age-appropriate complementary feeding^e^						✓^e^	✓	
Minimum dietary diversity						✓	✓	✓
Minimum meal frequency						✓	✓	✓
Minimum acceptable diet						✓	✓	✓
Anthropometry		✓	✓	✓	✓	✓	✓	✓
Acute respiratory infection			✓	✓	✓	✓	✓	✓
Acute diarrhea			✓	✓	✓	✓	✓	✓
Visit to emergency room			✓	✓	✓	✓	✓	✓
Hospitalization			✓	✓	✓	✓	✓	✓
mHealth usability								
Assessment								✓

a ✓ indicates step conducted or outcome measured at the specific time point.

b mHealth: mobile health.

c SoC: standard of care.

d IYCF: infant and young child feeding.

e The 6-month assessments of exclusive breastfeeding and age-appropriate complementary feeding will serve as the primary outcome.

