#### Primary Outcomes

The primary end points of the study are (1) EBF at 6 months of infant age and (2) introduction of AACF [49,50] at 6 months of infant age.

In addition, EBF will also be assessed at the 6th, 10th, and 14th weeks, while CF practices will also be assessed at 9 months of infant age. The repeated assessments at additional time points will be used for longitudinal analyses to evaluate trends and sustainability of feeding practices over time. Operational definitions of the primary outcome measures are provided in Table 3.

**Table 3. T3:** Operational definitions of primary and secondary outcome measures.

Outcome	Operational definitions
Primary outcomes [49,50]	
Exclusive breastfeeding	Proportion of infants who are fed exclusively with breast milk up to 6 months of age
Introduction of age-appropriate complementary feeding	Proportion of infants who are introduced to solid, semisolid, or soft foods at 6 mos of age
Secondary outcomes	
Infant and young child feeding practices [49,50]	
Early initiation of breastfeeding	Proportion of children put to the breast within 1 hour of birth
Minimum dietary diversity	Proportion of children 6‐12 months of age who receive food from 4 or more food groups
Minimum meal frequency	Average number of daily meals for children 6‐12 months of age, who receive solid, semisolid, or soft foods
Minimum acceptable diet	Composite variable based on meal frequency and dietary diversity
Mean duration of breastfeeding	Average duration an infant is breastfeeding for 12 months
Continued breastfeeding at 1 y	Proportion of children 12 months of age who are still on breast milk
Child health	
ARI^a^	Short, rapid breathing that is chest-related and/or difficult breathing that is chest-related. Percentage of children up to 1 year of age with symptoms of ARI at any time in the last 2 weeks preceding the follow-up
Acute diarrhea	Passage of 3 or more loose or liquid stools per day (or more frequent passage than is normal for the individual). Percentage of children up to 1 year of age with symptoms of diarrhea at any time in the last 2 weeks preceding follow-up
Visit to the emergency room	Infant brought to the emergency room for management of any acute illness in past 2 weeks.
Hospitalization	Infant admitted to the hospital for diagnosis or management of any acute illness in past 2 weeks.

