### Limitation

We acknowledge limitations in our study. First, participation is limited to literate women who own smartphones, which may restrict generalizability. However, this criterion is necessary to ensure valid exposure to the digital intervention and to evaluate its feasibility under real-world conditions. Second, despite restricted onboarding and backend access controls, some degree of information sharing between intervention and control participants may occur in community settings. Such contamination will be monitored through usage analytics and addressed analytically using intention-to-treat and sensitivity analyses. Third, behavioral outcomes may be subject to recall or social desirability bias. To mitigate this, standardized questionnaires, repeated assessments, and objective app usage metrics will be used where feasible. Fourth, sustained engagement with the app over the 1-year intervention period may decline due to digital fatigue or competing demands. Automated reminders and regular RA contact are incorporated to support adherence and maintain engagement. Fifth, blinding of participants and research staff is not feasible due to the nature of the intervention, which may introduce observer or reporting bias. However, this risk will be minimized through standardized outcome assessment procedures, structured questionnaires, RA training, and blinded data analysis using coded group allocation. Finally, the study assesses intervention effectiveness over a 1-year period and does not evaluate long-term sustainability or scalability. Findings will inform future studies designed to assess broader implementation and longer-term impact.

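### The abstract defines compliance as completing a 6-month coaching program, but the Methods describe coaching to 12 months of infant age, so the reported rate would cover about half of the course

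*Protocol article*

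**What the plan says.** The Methods paragraph of the abstract holds the only rule given under the name of compliance: "Compliance will be determined by the proportion of participants who complete the 6-month coaching program". It does not say when the 6 months start or what counts as completing.

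The body describes a longer course:

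- Message Schedule: "Messages will be delivered 3 times per week, beginning in the predelivery period and continuing until the child reaches 12 months of age".
- Table 2: "mHealth coaching will occur continuously across the study period", with visits to 12 months.
- Table 1: a complementary-feeding message stage covering 6 to 12 months.
- Limitation: "sustained engagement with the app over the 1-year intervention period may decline due to digital fatigue or competing demands".

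Two other sections bear on exposure. User Engagement Metric plans app analytics: "These metrics will provide an objective, time-stamped record of participant interaction with the intervention". Intervention Fidelity Assessment sorts participants into high, moderate and low groups: "Fidelity will be evaluated through cumulative exposure to scheduled content", together with modules completed and duration of use. It adds: "These fidelity classifications will allow examination of dose-response relationships between intervention exposure and primary outcomes". Those outcomes are fixed at one age: "The primary end points of the study are (1) EBF at 6 months of infant age", and likewise for the introduction of complementary feeding.

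**The concern.** The abstract names a program that the Methods do not describe, and nothing in the article explains the difference. If the sentence is followed, a mother who stops using the app when her infant is 6 months old can be counted as having completed the program, with the 6 to 12 month stage still ahead of her. The rate would say nothing about receipt of the messages aimed at dietary diversity, meal frequency and acceptable diet at 9 and 12 months, or at continued breastfeeding at 1 year. The Limitation section itself expects engagement to fall over the year, so the uncounted part is where non-adherence is most likely.

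A related but separate point concerns the fidelity groups. They are to be related to outcomes measured at 6 months, yet the article gives no cut-off for the content counted. Content viewed after the 6-month assessment cannot affect its result.

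**Working it through.** **Inputs from the article.** Three messages per week, ending at 12 months of infant age (Message Schedule). Enrollment at 35 to 37 weeks of gestation (Inclusion Criteria). App installed at enrollment (Application Onboarding). Visit window of 2 weeks either side (Follow-Up). Fidelity cut-offs of 70% and 40% of scheduled content (Intervention Fidelity Assessment).

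**Assumptions.** Delivery at 37 to 42 weeks, which the article does not give. A year is taken as 52 weeks and 6 months as 26. The rate of three messages per week holds throughout.

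**Length of the course.** Let p be the number of weeks from enrollment to delivery. The smallest value is 37 − 37 = 0, the largest is 42 − 35 = 7, and the middle case is 40 − 36 = 4.

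- Whole course: 3(p + 52) messages
- Six months counted from enrollment: 3 × 26 = 78 messages
- Up to 6 months of infant age: 3(p + 26) messages

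| p | Whole course | 6 months from enrollment | To 6 months of infant age |
|---|---|---|---|
| 0 | 156 | 78 (50.0%) | 78 (50.0%) |
| 4 | 168 | 78 (46.4%) | 90 (53.6%) |
| 7 | 177 | 78 (44.1%) | 99 (55.9%) |

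The plan's 6 months is therefore not reproduced as the length of the course, which is 52 to 59 weeks. A 6-month window takes in 44% to 56% of the messages.

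**The 6 to 12 month stage.** This is 26 × 3 = 78 messages, or 44.1% (78/177) to 50.0% (78/156) of the course. Six months from enrollment ends at an infant age of 26 − p, that is 19 to 26 weeks, so none of the stage is covered. Counting to 6 months of infant age also covers none. If the window closes at a 6-month visit held 2 weeks late, 2 × 3 = 6 of the 78 messages fall inside it (7.7%).

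**Fidelity groups, conditional illustration.** Suppose the groups were computed over the full schedule and each message counted as one equal unit of content.

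- A mother who views everything to 6 months of infant age and nothing later has viewed 50% to 56% of the content. That is the moderate band, although she received all the exposure that could affect the primary outcomes.
- A mother who views everything after 6 months reaches 70% overall if her share before 6 months is (0.7 × 3(p + 52) − 78) / (3(p + 26)). For p = 0 this is (109.2 − 78)/78 = 40.0%. For p = 7 it is (123.9 − 78)/99 = 46.4%.

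The second case meets only the content part of the high band, which also requires at least 70% of modules completed.

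**The case against.** The strongest reply is that this is one sentence about a descriptive figure. The Statistical Analysis section never uses it, and a 6-month window suits primary end points fixed at 6 months. Full-course exposure will also be available from the logs and the fidelity groups. Most of this stands. It limits the consequence, and it means the 6-month window as such is not an error. It does not rescue the wording: the abstract does not speak of exposure up to the primary end point but of completing the program.

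Four stronger readings are tempting, and the documents do not support them.

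- A reader might infer that adherence after 6 months will go unmeasured. The planned log-based measures have no 6-month limit.
- A reader might infer that the compliance rate and the fidelity groups contradict each other. The abstract sets no message-count rule for completion, so the two are different measures and may class the same mother differently.
- A reader might infer that the dose-response analysis will include exposure after the outcome. The article only leaves the cut-off unstated, and time-stamped data can be cut at the 6-month visit. An analysis plan that is not shown may do so.
- A reader might infer that the primary comparison is affected. It is not.

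It is also fair that narrow percentage ranges would claim too much, because the delivery date is assumed and the article gives no counts of content or modules.

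**Conclusion.** The inconsistency is real. The abstract's 6-month program conflicts with Table 1, Table 2, Message Schedule and Limitation, which agree on coaching to about 12 months of infant age. As worded, the compliance rate would be presented as program completion while covering about half of the scheduled messages and none or almost none of the 6 to 12 month stage. The phrase "about half" holds under either starting point and any delivery from 37 to 42 weeks. It describes the schedule, not what any participant will view.

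This is more than a slip of wording, because a reported result would carry the wrong label. It is still modest: the intention-to-treat estimates, the sample size and alpha do not change. The missing cut-off for the fidelity groups is a separate, conditional point, worth settling in the same correction.

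**What to change.** Correct the abstract's sentence to the 12-month course described under Message Schedule. From the app logs, report exposure over two windows, each labelled:

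- to the 6-month visit, beside the primary outcomes;
- to 12 months of infant age, beside the 9- and 12-month outcomes.

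For the dose-response analysis against the primary outcomes, state that only content scheduled and viewed up to each participant's 6-month assessment counts.

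The cost is one corrected sentence, one added line for the fidelity groups and one extra table from data already planned. Recruitment, visits and the primary analysis stay as they are. The drawback for the trial team is that the 12-month figure may be lower than the 6-month one. At the abstract's status date of 18 May 2026, 15 weeks after recruitment opened on 2 February 2026, no infant of a woman enrolled during pregnancy could yet have reached 6 months. At that date the correction could still precede every 6-month outcome.

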**Results:**

The study was approved by the Ethics Review Committee of the Aga Khan University and the National Ethics Committee. Participant recruitment started on February 2, 2026. As of May 18, 2026, 241 participants have been recruited. Follow-ups and outcome assessments are expected to be completed by June 2027.

**Conclusions:**

If effective, the *Pehli Ghiza* intervention could support the integration of digital health tools into standard of care in Pakistan and similar low- and middle-income country settings.

## Introduction

Undernutrition remains a critical global health issue, contributing to approximately 35% of the global disease burden [1] and accounting for 11% of all disability-adjusted life years [1]. It is associated with nearly half of all deaths among children younger than 5 years in low- and middle-income countries (LMICs) [2]. In Pakistan, the prevalence of stunting among children younger than 5 years remains alarmingly high at 40.2% [3], nearly double the regional average of 21.8% [4]. Wasting has increased from 8.6% (1997) [3] to a peak of 17.7% (2018) [3], significantly surpassing the World Health Organization (WHO) threshold of ≥5% for a public health emergency [5]. These deficits are reflected in the country’s high infant (50/1000 live births) [6] and under-5 (58/1000 live births) [6] mortality rates. Beyond health, the economic burden of undernutrition in Pakistan is substantial, costing an estimated 3% to 4% of the national gross domestic product due to lost productivity, increased health care expenditures, and diminished human capital [7].

Evidence shows that optimal infant and young child feeding practices (IYCFPs) are among the most effective interventions to prevent malnutrition and improve child survival [8]. These refer to early initiation of breastfeeding (EIBF) within 1 hour of birth, exclusive breastfeeding (EBF) for the first 6 months of life, and introduction of adequate and safe age-appropriate complementary foods (AACF) at 6 months, together with continued breastfeeding up to 2 years of age [9].

Despite modest progress, significant gaps persist in Pakistan’s infant and young child feeding (IYCF) indicators. The recent National Nutritional Survey reported improvements in EIBF from 40% (2011) [10] to 45% (2018) [3]; yet, nearly 40% of neonates continue to receive prelacteal feeds [3], undermining the benefits of colostrum feeding. Further, a nonlinear trend was found in EBF, decreasing from 50% (2001) [3] to 37.7% (2011) [10] before rising to 48% (2018) [3], reflecting inconsistent policies and nonsustainable interventions. The decline in EBF was particularly evident at 3 months of infant age, dropping from 84% to 70% [11], reportedly due to inadequate maternal knowledge about EBF and its associated benefits [12]. The continued breastfeeding practice at 1 year also declined from 77.3% (2011) [10] to 68.4% (2018) [3], with only 40.1% of children aged 0 to 23 months receiving age-appropriate breastfeeding [3]. This means that while initial breastfeeding practices may be improving, their maintenance and adherence remain inadequate and challenging. Further, the complementary feeding (CF) indicators were even more concerning. Only 36% of children aged 6‐8 months receive timely CF; minimum dietary diversity (MDD) is achieved by 14%, minimum meal frequency (MMF) by 18%, and a mere 3.6% of children meet the minimum acceptable diet (MAD) criteria [3], a composite indicator reflecting both meal frequency and diversity. These significant deficiencies impair infant physical growth, immunity, and cognitive development.

This alarming situation has not improved much, as a recent study conducted in rural Sindh Province reported that <10% of infants were EBF, with a significant proportion identified as wasted (14.7%), stunted (36.7%), and underweight (38.5%) at birth [13]. The study also found a significant association of early initiation of CF or breast milk alternatives before 4 months and increased odds of wasting by 6 months of age (adjusted odds ratio 4.14, 95% CI 1.95-8.77; *P*<.001) [13]. This further reflects persistent gaps in early child nutrition, which are the result of a complex interplay of inadequate maternal knowledge, sociocultural norms and myths, and insufficient nutritional counseling at health system touchpoints [14-16].

Addressing these gaps requires scalable, contextually appropriate, and sustainable strategies extending beyond established practices. The traditional approaches relying on face-to-face (F2F) nutritional counseling, whether facility-based or through community health workers, remain resource-intensive and face challenges of reach, quality, and sustainability. In this regard, mobile health (mHealth) interventions are promising tools, particularly for LMICs with limited health care resources [17]. Pakistan has experienced rapid digital expansion. Household internet access has increased from 34% (2018) to 70% (2025) [18], and individuals using the internet have increased from 17% (2018) to 57% (2025) [18]. Smartphone penetration has risen from 10% (2014) [19] to 64% (2024) [20], while 96% of households reported ownership of a mobile phone or smartphone [18], corresponding to 196 million cellular subscribers [21]. The majority of these users (77%) are young adults aged 21 to 30 years [22], representing a critical entry point for digital health interventions among this receptive population.

Studies have been conducted to evaluate mHealth in promoting optimal feeding practices. A mobile-based approach among teenage mothers in Nigeria reported an increase in knowledge scores about IYCFPs from 38.7% to 76.1% and in EBF practice from 49.3% to 63.5% at 6 weeks postintervention [23]. An mHealth intervention in Nepal improved maternal IYCF knowledge scores (β=.21, 95% CI 0.08‐0.35) and dietary diversity, primarily for egg consumption (odds ratio 1.36, 95% CI 1.07‐1.73) [24]. In Indonesia, an mHealth intervention resulted in a 1.45-fold increase in overall IYCF knowledge [25]. In rural Pakistan, a 14.8% increase in overall IYCF knowledge delivered via text messages was reported among mothers [26]. A prospective cross-sectional survey to evaluate the utility of *LactApp*, a mHealth app about breastfeeding, showed that users were satisfied (87.8%), felt assisted (75.3%), and supported (80.9%) in their experience [27].

However, these studies are limited by a predominant focus on knowledge enhancement rather than sustained behavioral change or long-term feeding practices. Evidence regarding the effectiveness of mHealth interventions on clinically meaningful IYCFPs remains inconsistent. For instance, a cluster randomized controlled trial (RCT) conducted in South Ethiopia demonstrated a significantly higher probability of maintaining EBF at 6 months in the intervention group compared to the control group (adjusted hazard ratio 0.40, 95% CI 0.26‐0.62; *P*<.001) [28]. Similarly, a quasi-experimental Australian study evaluating the Growing Healthy infant feeding app reported reduced health service utilization among app users, including lower odds of using one or more health services (odds ratio 0.38, 95% CI 0.25‐0.59), fewer visits to general practitioners (1.0 vs 1.5 visits; *P*=.003), and fewer pediatrician visits (0.3 vs 0.4 visits; *P*=.049), although no significant differences in out-of-pocket costs were observed [29]. Conversely, another RCT conducted in the United States evaluating the Breastfeeding at Augusta University smartphone app found no statistically significant differences in breastfeeding duration or breastfeeding self-efficacy between the intervention and control groups [30]. Mothers in the intervention arm breastfed for 10.1 (SD 3.5) months compared with 8.9 (SD 4.1) months in the control arm (*P*=.32), while antepartum and 1-year postpartum breastfeeding self-efficacy scores also did not differ significantly (*P*=.96) [30]. These contrasting findings suggest that the effectiveness of mHealth interventions may depend on specific intervention components, contextual adaptation, engagement strategies, and the intensity of participant interaction.

Systematic reviews further highlight persistent evidence gaps. Reviews of studies conducted in LMICs have reported inconclusive evidence regarding CF practices, dietary diversity, and sustained IYCF outcomes [31-33]. Another systematic review and meta-analysis evaluating digital health interventions versus standard care for improving EBF duration among postpartum mothers in LMICs identified substantial heterogeneity across studies (*I*²=77%) in intervention components, study designs, and outcome measures [34]. Collectively, these findings underscore the limited availability of rigorous, contextually tailored, and longitudinal evidence regarding the causal effectiveness of mHealth interventions in improving sustained breastfeeding and IYCFPs, particularly in low-resource settings.

In Pakistan, while cross-sectional surveys have examined the use of mobile technology in the broader maternal and child health domain [35-38], no RCT has rigorously evaluated the effectiveness of a culturally tailored mHealth intervention on sustained IYCFPs. Consequently, there is a lack of high-quality evidence to inform the integration of digital tools into national nutrition programs. Given Pakistan’s high burden of undernutrition, suboptimal feeding practices, and expanding digital infrastructure, this study aims to evaluate the efficacy of a culturally tailored mHealth coaching app, *Pehli Ghiza* (“first diet”), in promoting EBF and age-appropriate IYCFPs among mothers during the first year of infant life, generating actionable evidence for national nutrition strategies and policy in Pakistan and similar LMIC settings.

